#### Patient inclusion criteria

2.2.2

1.The patient is sentenced to in-patient forensic mental health care, in accordance with the Swedish judicial framework. In practice, this means that they have committed a crime warranting incarceration and that they have been found to suffer from serious mental illness in a forensic psychiatric evaluation.2.The treating psychiatrist and treatment team at each ward must approve of participation before the potentially participating patient is given information on the study. They will be instructed to base this approval on the basis of whether or not this patient can participate in IMR and is capable of giving informed consent. Examples of such factors rendering informed consent and thus participation not possible include presence of severe active psychotic symptomatology or severe intellectual impairment. The treating psychiatrist and treatment team will have ultimate veto rights if they for some other reason think that the participation of a patient in the project is not advisable on ethical grounds or because of mental health considerations.

We do not require that study participants fulfill any specific diagnostic criteria. Given that a large majority of patients within the Swedish forensic mental health services suffers from either a schizophrenia spectrum or bipolar disorder we consider it highly likely that a majority of our sample will present these disorders as their main diagnosis. However, it is also likely that some of the patients in our sample will have autism or mild intellectual impairment as their main diagnosis. This is in line with previous research on IMR, where a majority of patients included has suffered from either schizophrenia spectrum or bipolar disorders, and a minority of participants has suffered from other forms of mental illness (see for example [11,12,16]).

#### Staff inclusion criteria

2.2.3

1.The only requirement for staff participating in the part of the study focused on implementation processes is that staff participants are directly involved in administering IMR treatment and that they give informed consent to study participation. Participation in the study will not be a requirement for staff administering the treatment.

#### Intervention administered to patients in active condition (IMR)

2.2.4

IMR was developed as a treatment method targeted towards people with severe mental illness, within the framework of the Evidence-Based Practice Implementation Project [9]. It is a curriculum-based program combining elements from evidence-based practices such as cognitive-behavioral therapy, motivational interviewing and psychoeducational practices, in an effort to help patients achieve better illness self-management and subjectively meaningful recovery goals. The curriculum is organized around chapters pertaining to subjects such as social support, problem solving, medication, subjective recovery and relapse prevention. These chapters involve both educational material discussed during treatment sessions and material suitable as homework assigned for in-between session work [9]. Some adaptions have been made to the material to ensure the suitability of the treatment to the forensic setting. These include exclusion of two chapters in the original treatment program. These two chapters deal with healthy lifestyle choices and navigating the health care system. The first of these chapters has yet not been translated to Swedish in an adequate fashion and the second was deemed not relevant to the Swedish context. Instead, a special chapter has been written explaining the process of forensic mental health care from a patient perspective, adapted to the applicable regulatory framework. In the other chapters included in the study, certain examples and practical exercises have been modified to ensure applicability within the forensic context. Adaptions of the original material were made as part of a pilot study (not yet published) within a Swedish forensic mental health in-patient facility. Prior to this pilot study, permission for these adaptions was obtained by the developers of IMR.

Treatment is planned to take place during two group meetings and one individual follow-up meeting per week. Group meetings will be used to discuss and work with new treatment material, share experiences amongst group members, monitor progress towards subjectively meaningful recovery goals and set homework assignments for the next group session. Individual sessions will be used to repeat and clarify information given at group sessions, tailor homework to the individual patient, support completion of homework and efforts towards achieving recovery goals. The IMR material does not state a set number of sessions for the treatment, instead the material is worked through in a pace adapted to the patients receiving treatment. However, based on our experience we estimate that the active treatment phase will last for approximately nine months. Treatment sessions will be led by the forensic mental health staff at the wards participating in the active condition (i.e. psychiatric nurses and auxiliary psychiatric care-givers). Staff administering IMR-treatment will receive two full days of training in the method, as well as a weekly supervision session during the treatment period. Training in IMR will consist of lecture style presentation of information about treatment goals and contents as well as practical exercises in using methods included in the treatment material. During training sessions, participating personnel will also be encouraged to discuss how IMR can be optimally integrated in the daily routine of clinical work. The supervision sessions will consist of 1 h weekly meetings in a group setting, focusing on solving problems emerging in treatment as well as rehearsing and emphasizing treatment goals. This training and supervision will be provided by members of the research team, mainly KS and PA. During the treatment phase, responsibility for practically leading and implementing IMR will be the staff leading and planning daily work at the ward in question (i.e. the person or persons holding leadership positions at the ward participating in the treatment condition). The caseload of individual treatment providers could vary somewhat depending on variability in staffing and local decisions regarding the division of tasks at individual treatment sites. Based on the length of the IMR-program and estimations of staffing at an inpatient facility, we estimate that the mean number of group and individual session provided by individual staff at wards in the active condition will be approximately 5 and 10, respectively. The IMR treatment integrity scale (IT-IS) [17] will be used to assess treatment fidelity in the active condition, which is described in further detail below.

#### Control condition

2.2.5

Participants in the control condition will be given treatment as usual (TAU) during the study period. After completion of the study, participants in the control conditions will be offered participation in IMR if this is found more effective than TAU, conditional on them still being in-patients at the facilities participating in the study. Since the study will be conducted at different treatment sites, standard treatment given to participants in the control condition might differ somewhat. The TAU at each control site will be documented. In some cases, staff working at wards in the active condition and who thus have received training in IMR, might sometimes work at a ward in the control condition (for instance, in situations when there is a need to solve a shortage of staff).

#### Measures to avoid contamination

2.2.6

To avoid contamination between the active and control conditions, we will avoid training staff that regularly work at both active and control clusters. Some instances of staff trained in IMR working at control wards can probably not be avoided (e.g. in instances were acute staff shortages have to be addressed). Since IMR is a structured group intervention, this will not mean that participants receive the intervention in its intended group format. However, one clear risk is that staff trained in IMR apply the interventions and material from IMR in an ad hoc manner. To avoid this, trained staff will be instructed not to use IMR materials or interventions in cases where they are working at control wards. Instances of staff trained in IMR working at control wards will be documented. Staff at active and control wards will be instructed not to share information on the intervention during the trial and will be given a clear rationale for this. Furthermore, management at control wards will be interviewed about the contents of care at the ward during the trial period after the conclusion of the study, to assess whether or not substantial contamination occurred.

### Measurements

2.3

Assessment of outcome measures will be conducted at four time-points (at baseline, four-months into treatment, upon treatment completion and three months after treatment completion, see Table 1). To gather data pertaining to our secondary objective, semi-structured interviews as well as self-report measures completed by staff working at wards in the active condition will be collected. Assessment of the experiences of staff administering IMR will be gathered after completion of training but before treatment commencement, three months into treatment and a year after treatment commencement. In addition to this, audio from two IMR-sessions per group in the active cluster will be recorded and assessed with a fidelity measure. More details on the measures used in the study is outlined below.

**Table 1 tbl1:** Overview of evaluation plan.

		**Timepoint**			
		**Baseline (pre-treatment)**	**During treatment**	**Treatment completion**	**Post-treatment follow up**
**Outcome measures**	WHODAS	X		X*	X
	IMRs	X	X	X	X
	ASHS	X	X	X	X
	HoNOS-S	X		X*	X
**Process measures**	IT-IS		X		
	NoMAD	X	X		X

**IMRs** = Illness management and recovery scale, **ASHS** = Adult State Hope Scale, **WHODAS**= World Health Organization Disability Assessment Schedule, **HoNOS-S**= Health of Nation Outcome Scale-Secure, **IT-IS**= IMR Treatment Integrity Scale, **NoMAD**=Normalization Process Theory Measure. **IMRs** and **WHODAS** include both client and clinician rated versions of these scales. Post-treatment follow up is planned at three months after treatment completion. Time points for measurement during treatment differs between outcome measures and process measures. * = Denotes a primary outcome measure.

#### Background factors of the participants assessed before treatment commencement

2.3.1

To describe our sample and explore potential moderators of treatment outcome, information on some background characteristics of our sample will be collected, as described below.

#### Demographic measures

2.3.2

Participant's age, sex, diagnoses and when the participant underwent a forensic psychiatric evaluation and was admitted to the forensic mental health services will be assessed through extracting this data from the participants’ medical records.

#### Static criminogenic risk

2.3.3

With the aim of partially answering the second of our main objectives, the presence of static (i.e. historical) risk factors for criminal recidivism will be assessed through the medical records of participating patients. The static criminogenic risk factors assessed include the patient's number of previous convictions before admission into the forensic mental health services, index crime (most severe offense) in the trial that resulted in admission, age at first known criminal conviction, known history of substance abuse and whether or not there is evidence of criminality before the first known onset of symptoms of serious mental illness. Serious mental illness in this context refers to the main diagnosis that was assigned to the patient at the forensic psychiatric evaluation (in most cases this will mean before onset of first known active psychosis). Earlier research has indicated that such aspects can indicate increased risk of criminal recidivism and/or presence of traditional antisocial behavior patterns amongst offenders with serious mental illness [18,19].

#### Clinician assessed functional status

2.3.4

To further address the second of our main objectives, the functional status of participants in the active group will also be assessed, with anamnestic measures of functional status as well as a shorter neuropsychological test. The background measures pertaining to functional status are focused on historical role achievement/fulfillment. These include information on how the participants have earned an income before admission into forensic services, what their living condition was, their frequency of social contacts, educational attainment and relationship status. During the first assessment of the outcome measures (before treatment commencement) the participants will also complete a short neuropsychological test called the Zoo map, which is a subtest from the Behavioral Assessment of Dysexecutive Syndrome (BADS). The Zoo map subtest is designed to measure the ability to plan and monitor one's performance and compliance with pre-specified rules [20]. The person taking the test is tasked with drawing a route throughout a zoo, whilst complying with certain rules of how the route can be designed. Earlier research has shown that persons suffering from schizophrenia show impairments in this test, when compared to healthy controls [21]. Differences between persons suffering from schizophrenia with either acute symptomatology or in a more stable phase of disease progression have also been demonstrated [22]. In addition to this, participants will also be asked to rate their own performance, by answering four questions on a four-point scale. We expect that the administration of the Zoo test will add 5–10 min to the first assessment of outcome measures.

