The two main objectives are:1.To evaluate whether forensic patients receiving IMR show improvements on outcomes such as functional impairment, illness management ability, subjective recovery, sense of hope, and/or self-experienced functional status, when compared to a control group receiving treatment as usual.2.To evaluate to what extent the presence of background risk markers for criminal recidivism and/or the functional status of participants in the treatment group moderate effects of IMR on treatment outcome measures.

In addition, a secondary objective is:3.To explore how staff working with IMR experience the process of implementing the treatment.

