### Data analysis plan

2.4

Comparisons of primary outcome measures between the two conditions will be made on an intention to treat (ITT) basis. Linear mixed modeling (LMM) will be used to assess main effects of time, treatment and time by treatment interactions. A model based on observations nested within subjects, subjects nested within units and units within forensic settings will be evaluated. Models will be compared according to relevant indices of fit, such as AIC, BIC and Log-Likelihood. To test for group differences, post hoc-independent *t*-test will be performed at all time-points. Effect sizes will be expressed in Cohen's d.

In answering the second primary research objective stated above, pertaining to the influence (or non-influence) of potential moderating factors on treatment outcomes, multiple linear regression will be used as an analysis tool.

In regards to the secondary research objective, exploring the experiences of staff administering IMR, a mixed methods approach will be employed. In analyzing quantitative data from the S-NoMAD and change and stability over time on the four indexes of this instrument, linear mixed models will be employed. In analyzing data from the semi-structured interviews with staff, a qualitative approach will be employed.

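### Objective 2 asks whether functional status moderates the effect of IMR, but role history and the Zoo map are described for the active group only, so predictors of outcome under IMR cannot be told apart from moderators

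*Protocol article*

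**What the plan says.** The Introduction of the protocol article lists two main objectives. The first defines the effect of IMR as a comparison with a control group on treatment as usual (TAU). The second asks whether background risk markers and/or "the functional status of participants in the treatment group moderate effects of IMR on treatment outcome measures".

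Section 2.3.4 (Clinician assessed functional status) is written to serve that second objective. It states that "the functional status of participants in the active group will also be assessed", by means of role-history items (income, living conditions, social contacts, education, relationship status) and a short neuropsychological test. It adds that at the first, pre-treatment assessment "the participants will also complete a short neuropsychological test called the Zoo map", and puts the extra time at 5–10 minutes.

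Two neighbouring sections are worded differently. Section 2.3.3 says that static criminogenic risk "will be assessed through the medical records of participating patients", with no limit to one arm. Section 2.3.1, which introduces all the background measures, says that to describe the sample and "explore potential moderators of treatment outcome, information on some background characteristics of our sample will be collected".

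For the analysis, section 2.4 says of the moderator question only that "multiple linear regression will be used as an analysis tool".

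**The concern.** A moderator is a baseline factor across which the IMR-versus-TAU difference varies. To estimate that variation, the factor must be known in both arms. If it is known only among IMR patients, the analysis shows who does better or worse while receiving IMR. That includes patients who would have done better or worse on usual care anyway.

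The section on the Zoo map itself cites work in which performance differs between acute and stable phases of schizophrenia. A purely prognostic link with outcome is therefore a realistic possibility.

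At stake is the functional-status part of a main objective. The Discussion of the article presents the moderator work as informing providers' treatment decisions, so a predictor reported as a moderator could be used to decide who is offered IMR. A later analysis plan cannot repair this, because a pre-treatment test that controls never took cannot be recovered.

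**Working it through.** **Inputs from the article.** 80 patients, 40 per condition (section 2.2.1). Functional status in the active group only (Introduction, section 2.3.4). Zoo map 5–10 minutes (section 2.3.4).

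**Assumed inputs.** The article gives no prognostic correlation, no interaction size and no significance level for this analysis. I take two-sided 0.05, a standardised factor x, a control-arm outcome SD of 1, a main effect of 0.4 and no clustering.

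**The plan's own figure.** There is none for the moderator analysis. The only sample-size figure, 228 for the main effect, can be reproduced: 2 × (2.80/0.4)² = 98.1 per arm, times a design effect of 1 + 18 × 0.0085 = 1.153, gives 113.1, rounded up to 114 per arm, or 228. The intracluster correlation of 0.0085 is back-solved, since the article says only that it is small. This figure does not bear on the present point.

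**Identification.** Write the outcome as y = r·x + 0.4·T + g·x·T + error, with T = 1 for IMR and 0 for TAU. Here r is the prognostic slope and g the moderation.

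- Slope on x in the active arm: r + g.
- Slope on x in the control arm: r.
- Difference between the two, which is the interaction: g.

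With the active arm alone only r + g can be estimated. No modelling choice separates the two terms.

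**False signals (g = 0).** 20,000 simulated trials with 40 per arm; share with p < 0.05:

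| Assumed r | Active-arm slope only | Two-arm interaction |
|---|---|---|
| 0 | 5% | 5% |
| 0.2 | 24% | 5% |
| 0.3 | 47% | 5% |
| 0.4 | 74% | 5% |
| 0.5 | 92% | 5% |

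As a rough check at r = 0.3, the slope's standard error is about √(0.91/40) = 0.151, so the expected statistic is 0.30/0.151 = 1.99. That is close to the critical value, so a rate near one half is expected.

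The rate depends on the setting. At r = 0.1 the single-factor rate is about 9%. If the factor shares a model with 11 other independent predictors, the rates at r = 0.3, 0.4 and 0.5 fall to about 36%, 60% and 81%.

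**Masking (r = +0.3, g = −0.3).** The active-arm slope averages 0.3 − 0.3 = 0 and is significant in about 5% of trials. The interaction averages −0.30 and is detected in 27%.

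**What the two-arm test can do at N = 80.** Power for an interaction slope of 0.3 SD per SD is 25% (r = 0) to 27% (r = 0.3). The slope detectable with 80% power is 2.80 × √((1 − r²) × 2/40), which is 0.63 at r = 0 and 0.60 at r = 0.3.

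**Cost of control-arm data.** 40 × 5 to 40 × 10 minutes = 200 to 400 minutes, or about 3.3 to 6.7 hours.

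**The case against.** Four counter-arguments deserve an answer.

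1. *One-arm collection is not certain.* Section 2.3.1 speaks of the whole sample, and the Zoo map sentence refers to participants at a first assessment that both arms attend. This stands as an ambiguity. But the restriction appears in two specific places, the objective and section 2.3.4, which agree with each other, while section 2.3.1 is a general introduction. If both arms were intended, those two places are misworded and still need correcting.

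2. *Regression can test moderation.* A reader might infer from section 2.4 that choosing multiple linear regression is itself the error. The article does not support that. Regression with a product term is a standard moderation test, and the text neither specifies nor excludes one. Nor does its silence on wards, or on how many factors enter a model, show that clustering is ignored or that every candidate factor is fitted to 40 patients. Such detail is commonly left to a fuller document.

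3. *The whole of objective 2 fails.* A reader might infer this too, but it goes too far. Static risk factors come from records with no arm restriction, and baseline WHODAS, a measure of functional impairment, is likewise not limited to one arm. Both could be tested as moderators. WHODAS does not rescue the plan as written, because section 2.3.4 names other measures for this purpose.

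4. *The error rates are hypothetical.* They are. It cannot be said that the analysis will mislabel prognostic factors, only that it cannot distinguish them.

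**Conclusion.** The point holds for role history and the Zoo map. As the objective and section 2.3.4 are worded, no treatment-by-functional-status interaction can be estimated from these measures. The planned regression can identify predictors of outcome among IMR patients, not moderators of the IMR-versus-TAU effect.

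That conclusion follows from the one-arm measurement and needs no numerical assumption. Its practical size does. The illustrative range of 24% to 92% rests on assumed correlations of 0.2 to 0.5, one factor per model, 40 patients, no clustering and zero true moderation. Weaker prognosis or a fuller model lowers it.

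The primary comparison of IMR with TAU is untouched.

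**What to change.** Reconcile the second objective and section 2.3.4 with section 2.3.1 by stating that role history and the Zoo map are collected at baseline in both arms. Reword the objective so that functional status is not tied to the treatment group. In section 2.4, say that functional status will be tested through treatment-by-moderator terms, reported with confidence intervals and labelled exploratory in view of the low power at 80 patients.

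The cost is the Zoo map time for control patients, roughly 3 to 7 hours across the trial at a baseline assessment already planned, plus short history items and minor wording.

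If control data cannot be collected, restate this part of the objective as predictors of outcome among IMR recipients and make no moderation claim. That costs wording only.
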